## Abstract

**Background:**

Head and neck squamous cell cancer (HNSCC) has a poor prognosis, with approximately 25–30% of patients transitioning into the palliative phase at some point. The length of this phase is relatively short, with a median duration of five months. Patients in this stage often have increased prognostic information needs. Unfortunately, predicting individual life expectancy in this phase is particularly challenging, as physicians and patients tend to overestimate survival. To address this issue, we developed the prognostic model OncologIQ Palliative based on user preferences. In this study, we now aim to assess the clinical impact of utilizing this model during counselling.

**Methods:**

This study will employ both quantitative and qualitative approaches. The primary outcome is decisional conflict and satisfaction with the decision-making process after counselling without (cohort 1) and with (cohort 2) OncologIQ Palliative. Therefore, a prospective sequential cohort study will be conducted. Secondary outcomes include the amount of palliative treatment, overall survival rates, and quality of life. These measurements will be collected after the intervention. Additionally, patients’ perspectives on the decision-making process and proactive care planning, including end-of-life discussions, will be explored through interviews.

**Discussion:**

By offering more personalized prognostic information for HNSCC patients in the palliative phase, we anticipate a shift towards more patient-centred counselling. This approach can facilitate enhanced end-of-life discussions and better proactive care planning. Patients may experience reduced decisional conflict, feel better prepared for what’s coming, and find assistance in their decision-making process. This could potentially lead to fewer palliative treatments. Overall, these aspects can contribute to a better quality of life and quality of care for HNSCC patients in the last phase of their lives.

**Trial Registration:**

This study was registered November 18, 2024, on ClinicalTrials.gov: NCT06699316.

**Supplementary Information:**

The online version contains supplementary material available at 10.1186/s12904-025-01647-z.

## Background

### Background and rationale

Worldwide, head and neck squamous cell cancer (HNSCC) accounts for more than 700.000 new cases and 350.000 deaths annually [1]. In general, HNSCC has a poor prognosis, with over 40% of patients dying as a result of their disease [2]. Consequently, a large proportion of patients eventually reach the palliative phase [3], which begins when cure is no longer possible or when curative treatment is refused. In this stage, patients may experience specific problems such as dyspnoea, pain, psychosocial problems and the risk of a potential blowout [4–9]. 

The survival of patients with incurable HNSCC is relatively short, with a median of five months, although individual survival can range from one week to two years [10, 11]. Given this short length of the palliative phase, it is of key importance that patients have the best information available, such as accurate prognoses on quality of life (QoL) and life expectancy. Discussing prognosis and talking about death early in the disease trajectory enables patients to identify goals and make well considered end-of-life choices, which could contribute to a better QoL and quality of death [12, 13]. Studies have shown that patients who discuss end-of-life care with their physician are less likely to receive burdensome treatments, like chemotherapy, and more likely to receive hospice care [14, 15]. Some research even suggest that palliative or hospice care does not reduce survival and may actually prolong it [16, 17]. 

Despite patients’ desire for more detailed prognostic information [18–21], accurate individual life expectancy predictions for palliative HNSCC patients remain lacking. Physicians mainly rely on general estimates and their own experience, and their estimates are often inaccurate as they tend to overestimate survival [11, 22–26]. Additionally, physicians often feel uncomfortable and reluctant to discuss prognosis in the palliative phase, partly due to concerns about potentially being proved inaccurate [27]. Lack of accurate individual prognoses can result in suboptimal use of palliative and end-of-life care, and therefore, reduced QoL.

Besides meeting patients’ information needs, providing prognostic information in the palliative phase can influence their end-of-life choices. Decision making around treatment is challenging for both doctors and patients, often involving uncertainty and potential decisional conflict [28]. Personalized survival estimates allow for more realistic end-of-life discussions, enabling optimization of palliative care planning and impacting treatment decisions and participation in clinical trials [14, 15, 26]. 

Over the past years, a prognostic model named ‘OncologIQ’ for patients in the curative phase has been developed, validated, and recently updated with new prognostic factors [23, 29–31]. Unlike traditional survival rates based solely on TNM-classification, OncologIQ incorporates individual patient characteristics (such as age and the Adult Comorbidity Evaluation 27) to provide a more personalized estimate of the remaining life-span. Such prognostic models could aid physicians in delivering more accurate predictions of prognosis for individual patients. A recent clinical study demonstrated that counselling using OncologIQ improved decision-making [32]. However, until recently, a comprehensive prognostic model for palliative HNSCC patients was lacking.

To address this gap, we initiated the development of OncologIQ Palliative to predict individual survival for head and neck squamous cell carcinoma (HNSCC) patients in the palliative phase [33]. Recently, we validated, designed, and visualized it in an online dashboard [34, 35]. Our next step is to clinically test the effect of prognostic counselling using this model. We will investigate the impact of counselling patients without and with the prognostic model on decisional conflict and satisfaction with the decision-making process. Secondary aims include measuring satisfaction with proactive care planning after counselling with the prognostic model, as well as examining differences in terms of palliative treatment, overall survival rates, and QoL between cohorts.

### Methods/design

We will set up a single centre prospective sequential trial with two cohorts in a palliative HNSCC patient population. This study design is chosen in favour of a randomized controlled trial, because potential bias can be avoided as doctors develop a learning curve while working with the palliative model and could change their way of counselling. We aim to investigate the difference in effect of (prognostic) counselling without and with the use of OncologIQ Palliative by obtaining outcomes on decisional conflict, the amount of palliative treatment, palliative sedation or euthanasia, overall survival and QoL. The two cohorts in this study will be divided based on the type of prognostic counselling received. Cohort 1 will consist of patients who receive prognostic counselling without the model, reflecting the current clinical practice. Cohort 2 will comprise patients who receive additional prognostic counselling with the model. Additionally, we will conduct a qualitative evaluation through interviews among patients in cohort 2. This evaluation aims to investigate satisfaction with proactive care planning, including end-of-life discussions on preferred place of death and wishes for palliative sedation and euthanasia, following counselling with the use of OncologIQ Palliative.

Our hypothesis is that sharing personalized prognostic information on life expectancy with HNSCC patients in the palliative phase will empower patients throughout the decision-making process from the start of the palliative trajectory till death. More specifically providing this individualized prognostic information with the help of our prognostic model will lead to less decisional conflict and more satisfaction with the decision-making process. Additionally, we anticipate greater satisfaction with proactive care planning, including end-of-life discussions on preferred place of death and wishes for palliative sedation and euthanasia. Furthermore, when patients are optimally informed, they may choose palliative treatments less often, and it could lead to a higher QoL.

### Settings and participants

#### Settings

This prospective sequential cohort study will be situated at the Erasmus MC in Rotterdam, the Netherlands.

#### Participants and eligibility criteria

To be eligible for participation in the clinical study and qualitative evaluation, individuals must meet specific criteria. These include patients with HNSCC in the palliative phase and tumours situated in the oral cavity, oropharynx, nasopharynx, hypopharynx, supraglottic larynx, glottis larynx and unknown primary. Additionally, participants must have adequate understanding of the Dutch language and be aged 18 years or older. Exclusion criteria encompass individuals who are illiterate, have insufficient proficiency in the Dutch language, or lack decision-making capacity to consider their own treatment choices due to factors such as mental incapacitation.

### Sample size and power calculations

#### Clinical study

The power calculation is based on the primary outcome: decisional conflict. This implies that with an expected improvement on the decisional conflict scale of 8 points (out of 100), with a standard deviation of 17 points 79 patients per group are needed to find a statistical significant difference (α: 0.05; power: 0.80) [36]. Therefore we will include 160 patients in total, meaning *n* = 80 in each cohort. To our knowledge, there are no studies among palliative head and neck cancer patients who measure decisional conflict. Therefore, the study we used for estimating the standard deviation remains a ‘second best’ guess.

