To measure decisional conflict, patients will be asked to complete the Decisional Conflict Scale (DCS) questionnaire two weeks after the consult in which they received counselling. This can be done either online or by telephone. Therefore, the DCS is integrated into Healthcare Monitor, our electronic system for measuring patient-reported outcome measures (PROMs), enabling us to digitally send it to patients [37]. Data on QoL will be obtained using the EORTC QLQ-C15-PAL questionnaire, which is already included in Healthcare Monitor and is also part of our standard care for all patients with HNSCC in the palliative phase. The patient and tumour characteristics, such as smoking behaviour, ACE-27, and WHO-performance status will be collected at baseline. Additionally, data on palliative treatment, palliative sedation or euthanasia and overall survival will be gathered from the electronic patient files (EPFs).

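### The 79 patients per group cannot be reproduced from the printed inputs, which give 71 or 72; the article does not show whether 79 is an enrolment figure or rests on other inputs

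*Protocol article*

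**What the plan says.** All the inputs stand in the protocol article, under Sample size and power calculations, Clinical study. The effect is an "expected improvement on the decisional conflict scale of 8 points (out of 100"). The spread, the error rates and the resulting number follow in the same sentence: "with a standard deviation of 17 points 79 patients per group are needed to find a statistical significant difference (α: 0.05; power: 0.80"). The next sentence draws the recruitment target from that number: "Therefore we will include 160 patients in total, meaning" 80 in each cohort. The paragraph does not state sidedness, an allowance for loss or an adjustment for a non-parametric test. It does say that the standard deviation is a second-best guess, because no study in this population was found.

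Three other places bear on the point. Recruitment and study procedures sets the DCS "two weeks after the consult in which they received counselling". Background and rationale describes survival in this phase as short, "with a median of five months, although individual survival can range from one week to two years". Statistical analysis names a t-test, or a Mann-Whitney U test if the data are not normal, and plans multiple imputation for missing data.

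**The concern.** The paragraph prints every quantity that a two-sample comparison of means needs, so the result should follow from them. It does not: 79 is 7 or 8 patients per group above what the inputs give, which is too much for rounding of the result.

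At stake is what 79 means. If it already includes patients expected not to return a DCS, it is an enrolment number and the comparison itself needs fewer. If 79 returned questionnaires really are needed, some printed input is not the one that was used, and enrolling 80 leaves almost no room for death or non-response before the two-week questionnaire. The two readings lead to different answers on how many returned DCS forms deliver the stated power, and so on whether 80 enrolled per cohort are enough.

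**Working it through.** **Inputs.** Difference 8, SD 17, alpha 0.05 and power 0.80, all from the sample-size paragraph; two groups of equal size. Sidedness is not stated, so two-sided is assumed and one-sided also tried.

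**Attempt to reproduce 79.** Normal approximation:

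n per group = 2 × (1.960 + 0.842)² × 17² / 8² = 2 × 7.849 × 289 / 64 = 70.9, so 71.

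The two-sample t-test (noncentral t) gives 71.86, so 72. The stated 79 is not reproduced.

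**Power at the stated numbers** (t-test, difference 8, SD 17): 0.836 with 79 per group and 0.841 with 80.

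**Variants that keep the printed inputs.**

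| Variant | n per group |
|---|---|
| Two-sided, normal approximation | 71 |
| Two-sided, t-test | 72 |
| One-sided, normal approximation / t-test | 56 / 57 |
| Mann-Whitney, relative efficiency 3/π (71.86 / 0.955 = 75.2) | 76 |
| Mann-Whitney, 15% inflation (71.86 × 1.15 = 82.6) | 83 |
| Mann-Whitney, relative efficiency 0.864 (71.86 / 0.864 = 83.2) | 84 |

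None gives 79.

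**What does give 79.** Each of these adds or changes something:

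- A 10% loss on the normal-approximation figure: 71 / 0.9 = 78.9, so 79. The paragraph mentions no such loss.
- A smaller difference: 2 × 7.849 × 289 / 7.6² = 78.5, so 79 by the normal approximation. By the t-test the matching difference is about 7.63. Either would round to the printed 8.
- A larger SD: about 17.8 by the t-test. This would not round to 17.
- One-sided alpha 0.05 with 90% power: 78.03, so 79. This contradicts the stated power.

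**What each leading explanation leaves for loss.**

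- If 72 returned DCS forms are needed, 80 enrolled tolerate (80 − 72)/80 = 10% loss.
- If 79 are needed, 80 enrolled tolerate (80 − 79)/80 = 1.25%, one patient per cohort.

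**Power with 80 enrolled per cohort** (t-test). The loss rates are assumptions; the article gives none.

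| Loss before the DCS | DCS per cohort | Power, difference 8, SD 17 |
|---|---|---|
| 0% | 80 | 0.84 |
| 5% | 76 | 0.82 |
| 10% | 72 | 0.80 |
| 15% | 68 | 0.78 |
| 20% | 64 | 0.75 |

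If the true planning difference were 7.6 with SD 17, 72 returned forms would give a noncentrality of (7.6/17) × √(72/2) = 2.68 and a t-test power of 0.76.

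**The case against.** A reader might infer that the plan makes no allowance for loss before the DCS. The article does not support that. It is silent on loss, and 71/0.9 lands on 79, so a 10% allowance inside the figure is a leading explanation. An article may also leave a dropout rate to the full protocol, which is not shown. What stands is narrower: the paragraph calls 79 the number needed for significance, and if it contains an allowance, that label is wrong.

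A reader might also infer that 72 is the correct number and 79 a plain mistake. That goes too far as well. The inputs are printed as whole numbers, and a difference of 7.6 shown as 8 gives 79 with the printed SD. The source of the SD is not available here. The supportable statement is that 79 does not follow from the inputs as printed.

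Nor does the discrepancy show that the trial is underpowered. On the printed inputs it is conservative, and 80 per cohort hold 0.80 power after 10% loss. The article also admits that the SD is uncertain, and a modest change in the SD moves the number as much as the gap found here. This limits the consequence but does not make the printed figure reproducible.

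The short survival makes some early loss plausible, but the article gives no rate. Enrolled patients have attended, have capacity and have consented, and they may complete the DCS by telephone. A death rate read from the median survival would therefore be a soft figure, and the point does not rest on one. Multiple imputation shows that missing data were considered, but it does not restore the information lost with missing primary outcomes.

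**Conclusion.** The point holds as a defect in the stated sample-size basis. The printed inputs give 71 (normal approximation) or 72 (t-test) per group against the stated 79, and power of about 0.84, not 0.80, at 79 or 80. This assumes a two-sided test and equal groups; a one-sided test moves the result further from 79.

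The article does not settle which explanation applies. Under an undeclared 10% allowance, 79 is mislabelled and 80 enrolled are adequate up to 10% loss. Under different inputs, the printed ones are not those used and the margin is one patient per cohort. The planned total of 160 is not shown to be too small; what is missing is a basis from which a reader can judge it.

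**What to change.** Restate the sample-size paragraph so that the number follows from its inputs, and keep 160. The wording depends on how 79 arose, which the authors must establish.

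- **If the printed inputs stand:** state that 72 patients with a DCS per cohort give 80% power (two-sided alpha 0.05, difference 8, SD 17); that 80 are enrolled per cohort, which allows up to 10% without a DCS; and that power is 0.84 with no loss.
- **If other inputs produced 79:** print those inputs, and give the power that 80 enrolled per cohort deliver after the loss expected before the two-week DCS.

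In both cases, say whether 80 means enrolled or DCS-complete, and state the sidedness of alpha.

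The cost is one reworded paragraph and no change to the planned 160. The downside is that the 80% power becomes visibly conditional on DCS return: at least 90% if the printed inputs stand, and nearly complete return if 79 questionnaires are truly needed.

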### Qualitative evaluation

In cohort 2 we will use a purposive sampling method to select patients, striving for a reflection of the patient group in terms of sex, age and tumour location. There are no additional selection criteria for participating in the interview. We cannot calculate a specific sample size due to the qualitative design. Therefore, we will continue including patients upon data saturation is achieved.

### Recruitment and study procedures

#### Clinical study

Patients who are transitioning into a palliative HNSCC trajectory will be consecutively approached to participate in the study. The investigator will start by screening eligible patients after their first or follow-up visit. Once the patient has been discussed in the RWHHT, the researcher will check whether the palliative trajectory is confirmed.

In cohort 1, during the visit in which the palliative trajectory is discussed, the physician will provide counselling without the individualized prognostic model. As part of standard care, the patient will then visit the nurse practitioner immediately after their appointment with the physician. During this visit, the nurse practitioner or the investigator will inform patients about the study and present the subject information sheet. Patients will be asked to participate, and the informed consent (IC) form will be collected digitally.

In cohort 2, during the visit in which the palliative trajectory is discussed, the physician will inform the patient about the option to receive additional individualized prognostic counselling on their life-expectancy using OncologIQ Palliative. Considering that most patients have prognostic inquiries when discussing the palliative trajectory (*‘Doctor*,* how long will I live?’)*, we would like to offer them the model’s prognostic information directly or in a follow-up consultation, according to their preference. We believe it is unethical to let them wait for several days if they want to receive more prognostic information right away. If patients opt not to receive their individually calculated prognosis, they will be counselled without the model and offered general information about prognosis. However, if patients prefer not to receive any information on prognosis, their preference will be respected. As part of standard care, the patient will directly visit the nurse practitioner after their appointment with the physician. During this visit, the nurse practitioner or the investigator will provide the patient with additional oral information and the subject information sheet. We will only inform patients if they have received counselling with the model. If these patients wish to continue participating, we will ask them to sign the IC digitally.

To measure decisional conflict, patients will be asked to complete the Decisional Conflict Scale (DCS) questionnaire two weeks after the consult in which they received counselling. This can be done either online or by telephone. Therefore, the DCS is integrated into Healthcare Monitor, our electronic system for measuring patient-reported outcome measures (PROMs), enabling us to digitally send it to patients [37]. Data on QoL will be obtained using the EORTC QLQ-C15-PAL questionnaire, which is already included in Healthcare Monitor and is also part of our standard care for all patients with HNSCC in the palliative phase. The patient and tumour characteristics, such as smoking behaviour, ACE-27, and WHO-performance status will be collected at baseline. Additionally, data on palliative treatment, palliative sedation or euthanasia and overall survival will be gathered from the electronic patient files (EPFs).

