In conclusion, translating the different individual preferences into effective communication can be complex, and ensuring that patients comprehend these probabilities without causing undue confusion is a delicate task. To address these challenges, we previously conducted interviews with both patients and healthcare professionals to explore those differing topics [34]. By understanding their preferences and refining our communication strategies, we aim to optimize the delivery of this personalized prognostic information during the clinical study.

An unforeseen challenge arose from the unexpected requirement to comply with the Medical Device Regulation (MDR). Previously, it was not standard practice to adhere to *MDR regulations during the research phase*. This mandate added significant complexity to the study design and implementation process, as ensuring compliance with MDR regulations demands additional resources and specialized expertise. While the possibility exists that the final results of our study may not align with our initial expectations, potentially resulting in the model not being implemented as standard care.

Moreover, obtaining a CE marking for the final product poses difficulties. CE marking is essential for ensuring that medical devices comply with European Union (EU) regulations and standards, allowing them to be used within the EU. However, the strict requirements and evaluation processes associated with acquiring a *CE marking can be time-consuming and resource-intensive*. As a result, navigating the regulatory landscape for obtaining a CE marking is a significant operational challenge for our study team. To address these issues, careful consideration and planning were required to ensure compliance with MDR regulations and support the process of obtaining CE marking in the future. Instead of acquiring ethical approval for the entire project at once, we decided to divide our request in two. This was considered necessary to be able to start with the project without any further unnecessary delay. In the meantime, we are engaging with regulatory experts, allocating sufficient resources, and adjusting the study timeline to accommodate to these regulatory requirements.

Despite these challenges, we remain committed and are currently en route to overcome all regulatory hurdles to ensure the successful execution and dissemination of the study results through multiple publications.

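### Cohort 2 patients are informed of the study and asked to consent only after seeing their personal survival estimate, so entry may depend on their reaction to it and may bias the decisional conflict comparison

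*Protocol article*

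**What the plan says.** All of the following is in the protocol article, Recruitment and study procedures, Clinical study, unless another section is named.

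- **Cohort 1.** The physician counsels without the model, and the patient then goes straight to the nurse practitioner. "During this visit, the nurse practitioner or the investigator will inform patients about the study and present the subject information sheet." Consent is collected digitally.
- **Cohort 2, timing of the estimate.** The physician offers the model at the palliative-trajectory visit: "we would like to offer them the model’s prognostic information directly or in a follow-up consultation, according to their preference."
- **Cohort 2, study information.** At the nurse practitioner visit, "the nurse practitioner or the investigator will provide the patient with additional oral information and the subject information sheet". The condition attached is: "We will only inform patients if they have received counselling with the model."
- **Cohort 2, consent.** "If these patients wish to continue participating, we will ask them to sign the IC digitally."
- **Outcome and analysis.** The DCS is completed two weeks after the counselling consultation, and no DCS before counselling is described. Under Statistical analysis, the cohorts are compared by t-test or Mann-Whitney test, missing data are multiply imputed, and a multivariable regression of the total DCS uses patient and tumour characteristics. The sample size section assumes an 8-point difference, an SD of 17 and 80 patients per cohort.

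**The concern.** In cohort 2 the intervention comes first and enrolment second. A patient who is shocked or confused by the estimate can decline the study and then has no DCS score. A patient who found it helpful may be more willing to sign. Membership of the intervention cohort is thus partly decided after exposure.

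Cohort 1 does not escape this altogether, because its patients also consent after a difficult conversation. They have not, however, been shown an individual estimate. The cohort 2 trigger for refusal has no counterpart in cohort 1, and the two selections need not cancel.

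The planned analysis cannot repair this. Multiple imputation fills gaps for enrolled patients, not for people who never consented. The named covariates do not measure the reaction to the estimate. Without a DCS taken before counselling, there is no baseline on which to compare those who enter each cohort. If refusal is linked to distress, the study would also under-record the reactions it most needs to see.

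**Working it through.** The plan gives no refusal rate, so there is no figure of its own to reproduce. The 8-point target and the SD of 17 serve only as yardsticks.

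**Step 1: order of events.**

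| | Cohort 1 | Cohort 2, model accepted |
|---|---|---|
| Physician contact | Trajectory discussed, usual counselling | Trajectory discussed, model offered; estimate given then or at a follow-up consultation |
| Study information | Nurse practitioner visit directly afterwards | Nurse practitioner visit, conditional on having received model counselling |
| Consent | After usual counselling | After the estimate |
| Individual estimate seen before consent | No | Yes |
| DCS | Two weeks after counselling | Two weeks after counselling |

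**Step 2: bias formula.** In one cohort, let m be the mean DCS of those who consent, q the share who refuse because of their reaction, and D the amount by which the refusers' DCS would have exceeded m. The mean for everyone is (1 − q)m + q(m + D) = m + qD, so the observed mean is too low by qD. Lower DCS is better, and benefit is the cohort 1 mean minus the cohort 2 mean. The apparent benefit is therefore overstated by

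q2 × D2 − q1 × D1.

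**Step 3: illustration with q1 = 0.** This is the upper case for given q2 and D2, provided D1 is not negative. All q and D values are assumptions.

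| q2 | D2 | Bias (points) | Share of 8 points |
|---|---|---|---|
| 5% | 10 | 0.05 × 10 = 0.5 | 6% |
| 10% | 15 | 0.10 × 15 = 1.5 | 19% |
| 20% | 20 | 0.20 × 20 = 4.0 | 50% |

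D of 15 and 20 are 15/17 = 0.9 and 20/17 = 1.2 SD, so the last row is the strong end.

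**Step 4: adding the cohort 1 term.**

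- q2 = 20%, D2 = 20 with q1 = 10%, D1 = 15: 4.0 − 1.5 = 2.5 points in favour of the model.
- Equal q and D in both cohorts: 0.
- q2 = 5%, D2 = 10 with q1 = 10%, D1 = 15: 0.5 − 1.5 = −1.0, against the model.

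**Step 5: cross-check with a graded model.** Assume no true effect, normal scores with SD 17, 80 per cohort and no selective refusal in cohort 1. In cohort 2 the share q with the worst reaction refuses, and reaction correlates ρ with DCS. The false benefit is ρ × 17 × φ(k)/(1 − q), where φ is the standard normal density and k its upper-q point. For ρ = 0.5 and q = 20% this is 0.5 × 17 × 0.280/0.8 = 3.0.

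| ρ | q = 10% | q = 20% | q = 30% |
|---|---|---|---|
| 0.3: false benefit (points) | 1.0 | 1.8 | 2.5 |
| 0.3: chance of a significant result favouring the model | 6% | 10% | 16% |
| 0.5: false benefit (points) | 1.7 | 3.0 | 4.2 |
| 0.5: chance of a significant result favouring the model | 9% | 21% | 37% |

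The nominal chance is 2.5%. These figures also set cohort 1 refusal to zero, so they too are upper illustrations.

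**The case against.** The best reply is that refusal after bad news is possible in both cohorts, that nothing in the article links refusal to DCS, and that the direction is uncertain. A sobering estimate might settle a decision, and shock at a prognosis is not the same as decisional conflict. This stands. A reader might infer that cohort 2 *is* enriched for favourable reactions, but the documents support only that it *may* be. The cohort 1 term belongs in any estimate of size.

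The wording also leaves some room. The references to additional oral information and to continuing participation hint that the study might be mentioned earlier, and the article does not say which nurse practitioner visit applies to patients who choose a follow-up consultation. The procedure flowchart (Fig. 1) could not be consulted here. Even so, no consent step before disclosure is described, and the stated condition, read literally, places study information after it.

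Three further inferences are tempting and not supported:

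- *That the plan defends this consent order by the need to avoid delay, and that the defence fails.* The sentence "We believe it is unethical to let them wait for several days if they want to receive more prognostic information right away" justifies prompt disclosure of the estimate. The article gives no explicit reason for the consent order.
- *That using the model before consent conflicts with device regulation.* The remarks under Challenges and resolutions concern compliance and a divided ethics request. They say nothing about consent timing.
- *That this point covers patients who decline the model.* For them, "If patients opt not to receive their individually calculated prognosis, they will be counselled without the model and offered general information about prognosis." Their absence from cohort 2 is a separate selection and remains whatever the consent order.

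Moving cohort 2 consent forward could create a new asymmetry if cohort 1 had a different consent point. Anchoring both cohorts to the same nurse practitioner visit meets this for patients who choose a follow-up consultation. For patients who want the estimate at once, reordering the visit is more debatable, so the change should apply only where it is feasible.

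**Conclusion.** The point holds as a design risk. The article makes cohort 2 information conditional on having received model counselling and asks for consent afterwards, so enrolment can depend on the reaction to the intervention. Cohort 1 consents after usual counselling without an individual estimate. Selective refusal may therefore differ and may bias the unadjusted DCS comparison, possibly in favour of the model.

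The size is unknown. With cohort 1 refusal set to zero, assumed refusal of 5–20% and excess DCS of 10–20 points give 0.5–4 points, or 6–50% of the 8-point target. Selective refusal in cohort 1 of patients with higher DCS would reduce this and could cancel or reverse it. The analysis as described cannot detect or correct the problem, because refusers leave no data.

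**What to change.** 1. Set the same consent point in both cohorts: the nurse practitioner visit directly after the palliative-trajectory discussion.
2. In cohort 2, inform patients who choose the model in a follow-up consultation, and ask for their consent, at that visit, before the estimate is shown. This delays nothing and matches cohort 1.
3. For cohort 2 patients who want the estimate at once, inform them and ask for consent before disclosure where this is feasible the same day without holding back the information.
4. Replace the sentence that makes study information conditional on model counselling so that it agrees with items 1–3.
5. Record and report, by cohort, the numbers approached, refusing and withdrawing, and for cohort 2 whether each refusal or withdrawal came before or after disclosure.

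**Cost.** An amendment to the consent order, a simple log, and a slightly longer visit for some patients who want the estimate immediately. Earlier consent does not guarantee a DCS at two weeks, since a distressed patient can still withdraw or not respond. Such losses would then be counted among enrolled patients instead of going unseen.
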